## Abstract

**Background:**

Despite advances in treatment of people living with HIV, morbidity and mortality remains unacceptably high in sub-Saharan Africa, largely due to parallel epidemics of poverty and food insecurity.

**Methods/Design:**

We conducted a pilot cluster randomized controlled trial (RCT) of a multisectoral agricultural and microfinance intervention (entitled *Shamba Maisha*) designed to improve food security, household wealth, HIV clinical outcomes and women’s empowerment. The intervention was carried out at two HIV clinics in Kenya, one randomized to the intervention arm and one to the control arm. HIV-infected patients >18 years, on antiretroviral therapy, with moderate/severe food insecurity and/or body mass index (BMI) <18.5, and access to land and surface water were eligible for enrollment. The intervention included: 1) a microfinance loan (~$150) to purchase the farming commodities, 2) a micro-irrigation pump, seeds, and fertilizer, and 3) trainings in sustainable agricultural practices and financial literacy. Enrollment of 140 participants took four months, and the screening-to-enrollment ratio was similar between arms. We followed participants for 12 months and conducted structured questionnaires. We also conducted a process evaluation with participants and stakeholders 3–5 months after study start and at study end.

**Discussion:**

Baseline results revealed that participants at the two sites were similar in age, gender and marital status. A greater proportion of participants at the intervention site had a low BMI in comparison to participants at the control site (18% vs. 7%, p = 0.054). While median CD4 count was similar between arms, a greater proportion of participants enrolled at the intervention arm had a detectable HIV viral load compared with control participants (49% vs. 28%, respectively, p < 0.010). Process evaluation findings suggested that *Shamba Maisha* had high acceptability in recruitment, delivered strong agricultural and financial training, and led to labor saving due to use of the water pump. Implementation challenges included participant concerns about repaying loans, agricultural challenges due to weather patterns, and a challenging partnership with the microfinance institution. We expect the results from this pilot study to provide useful data on the impacts of livelihood interventions and will help in the design of a definitive cluster RCT.

**Trial registration:**

This trial is registered at ClinicalTrials.gov, NCT01548599.

**Electronic supplementary material:**

The online version of this article (doi:10.1186/s40064-015-0886-x) contains supplementary material, which is available to authorized users.

## Background

Despite major advances in care and treatment of those living with HIV, morbidity and mortality among people living with HIV/AIDS (PLHIV) remains unacceptably high in sub-Saharan Africa, largely due to parallel epidemics of poverty and food insecurity (Weiser et al. 2011). There are an estimated 35.3 million PLHIV worldwide, 70.8% of whom live in sub-Saharan Africa (Global report 2013). Food insecurity, defined as “the limited or uncertain availability of nutritionally adequate, safe foods or the inability to acquire personally acceptable foods in socially acceptable ways,” (Normen et al. 2005) is also highly prevalent in sub-Saharan Africa, where 240 million persons, or one in every four people, are estimated to be food insecure (FAO 2010). The prevalence of food insecurity is even higher among PLHIV in sub-Saharan Africa. Studies from Kenya and Uganda have shown that over 50% of PLHIV are moderately or severely food insecure (Mbugua et al. 2008; Weiser et al. 2010a).

Food insecurity and HIV/AIDS are leading causes of morbidity and mortality in sub-Saharan Africa and are inextricably linked, with each condition heightening vulnerability to, and worsening the severity of the other condition (Weiser et al. 2011). Food insecurity enhances HIV acquisition risk through increased risky sex and also increases susceptibility to HIV among those who are exposed (Weiser et al. 2007; Campbell et al. 2009; Webb-Girard et al. 2012; Weiser et al. 2011). Among PLHIV, food insecurity inhibits antiretroviral therapy (ART) initiation, retention in care, and ART adherence (Weiser et al. 2010b; Goudge & Ngoma 2011; Nagata et al. 2012; Weiser et al. 2009a; Wang et al. 2011; McMahon et al. 2011; Weiser et al. 2009b; Weiser et al. 2012). Food insecurity has been associated with a range of adverse clinical effects among PLHIV, including declines in physical health status (Weiser et al. 2009c; Weiser et al. 2012), decreased viral suppression (Weiser et al. 2009a; Kalichman et al. 2010a), worse immunologic status (Weiser et al. 2009c; Kalichman et al. 2010b), increased incidence of serious illness (Tsai et al. 2011), and increased mortality (Weiser et al. 2009b). In turn, HIV/AIDS worsens food insecurity by eroding economic productivity (Larson et al. 2008; McIntyre et al. 2006; Russell 2004), reducing social support due to HIV stigma (Tsai et al. 2011), and increasing medical expenses (McIntyre et al. 2006).

Although there has been a substantial increase in the allocation of international resources towards HIV care and treatment programs in Africa, food insecurity can significantly compromise the effectiveness of these programs due to its effects on morbidity and mortality as described above (Mamlin et al. 2009). As a result, the World Health Organization, UNAIDS and the World Food Programme have recommended integrating sustainable food production strategies into HIV/AIDS programming (Food and Nutrition Technical Assistance. HIV/AIDS: A Guide For Nutritional Care and Support; Nutrition and HIV/AIDS 2001; Blumberg & Dickey 2003; World Food Program 2003). Specifically, UNAIDS calls for international partners to “fund multisectoral HIV programming that incorporates effective food and nutrition interventions, in line with scale-up towards universal access to prevention, treatment, care and support” (UNAIDS Policy Brief 2008). Yet, little research exists to document the beneficial effect of food security or sustainable agricultural interventions on antiretroviral (ARV) adherence, HIV clinical outcomes, women’s empowerment and HIV transmission risk behaviors among PLHIV in Africa or elsewhere.

To date, no randomized controlled trials have been conducted in resource-limited settings to examine the impacts of either food supplementation or sustainable food production strategies on HIV morbidity and mortality (Mahlungulu et al. 2007). Several small studies in developing countries have demonstrated the potential for programs that address food security to affect health outcomes among PLHIV (Mamlin et al. 2009; Cantrell et al. 2008; Agricultural initiatives for health in Haiti; Ochai 2008; Njenga et al. 2009; Byron et al. 2008). Yet, existing intervention approaches to impacting food security have focused primarily on direct macronutrient supplementation, which may be somewhat limited in its scalability and sustainability (Sztam et al. 2010). Livelihood interventions, which address upstream causes of food insecurity, may have a better chance of improving health outcomes, and may be more sustainable. Similarly, while microcredit programs can improve health and prevent disease acquisition by targeting poverty and gender inequality (Ashburn et al. 2008; Kim et al. 2008; Schuler & Hashemi 1994), they have been criticized in terms of their effectiveness as a stand-alone strategy. As a result, experts have recommended integrating microfinance and other livelihood approaches to maximize HIV prevention and treatment efforts and reduce poverty (Dworkin & Blankenship 2009; Weinhardt et al. 2009). Income generating activities are well suited to improving food security (Diagne 1998; Doocy et al. 2005), and to retaining patients in HIV care (Mamlin et al. 2009; Gomez et al. 2004).

Following our previously published theoretical model (Weiser et al. 2011), we set out to test the impact of a multisectoral agricultural intervention on HIV health outcomes and transmission risk behaviors in rural Kenya. In a previous small feasibility study conducted by our group, we showed that using a human powered irrigation hip pump combined with a microfinance loan led to increases in crop yields, household income, CD4 counts and BMI (Pandit et al. 2010). In the current study, we developed and tested a modified version of this combination agricultural and microfinance intervention called *Shamba Maisha,* Kiswhahili for “farm life,” in a small community randomized control trial. In this study, we aimed to explore the acceptability and feasibility of the intervention and control conditions that will be used in a subsequent, larger cluster randomized controlled trial, and examined preliminary impacts on outcomes of interest. Two similar district hospitals in southern Nyanza Province were randomized: one to the intervention and the other to the control group. We hypothesized that this multisectoral intervention will improve food insecurity, household wealth and HIV health outcomes. We developed and tested a theoretical framework for the pathways through which this multisectoral agricultural intervention may improve health. In this paper, we described our conceptual framework, study methods, baseline findings, as well as process evaluation findings of successes and challenges with implementation.

## Methods

### Setting

The study took place in Rongo and Migori districts in Nyanza Province, Kenya. As of 2008, the HIV prevalence in Nyanza Province, Kenya, was estimated to be 15.3%, more than twice the national average (Kenya National Bureau of Statistics and ICF Macro 2010). Nearly all HIV-affected households in a recent Kenyan survey were considered to be moderately or severely food insecure (Mbugua et al. 2008). The province also has a significant shortage of accessible water making communities vulnerable to the impacts of drought, and a heavy dependence on an unstable agricultural sector. Farming and fishing are the primary means of income generation in Nyanza Province. Lack of irrigation and unpredictable rainfall leading to an inconsistent water supply remains a central barrier to successful farming for many in the region (Government of Kenya 2008).

### Description of intervention

The *Shamba Maisha* intervention consisted of three components: 1) a microfinance loan (~$150) to purchase the farming commodities, 2) a micro-irrigation pump, seeds, fertilizer and pesticides, and 3) trainings in sustainable agricultural practices and financial literacy. KickStart, an international non-governmental organization (NGO), along with technical support of agricultural experts from the University of California Davis, led the agricultural component of the intervention. *Adok Timo*, a microfinance institution in Nyanza Province, implemented the economic aspects of the intervention with support from the UCSF and KEMRI research team. The intervention components are described below.

#### Loan program

The microfinance loans were managed by *Adok Timo,* which has branches in Nyanza Province. The intervention group received training on financial management and marketing skills prior to receiving the loan. All trainings took place on participant’s farms or a nearby location. Participants were required to save 500 Kenyan shillings (~$6.00 USD) prior to receiving the loan. Each participant received vouchers to purchase the following items: the Hip Pump, 50 feet of hosing, fertilizer, and government certified seeds. These materials were purchased at a local farm store (“agrovet”). Loan repayment could begin at any time, but farmers were expected to make a minimum payment after the first harvest, usually 4–6 months after planting. Farmers were expected to repay in full by the end of two harvest seasons (approximately one year); however, if regular payments have been made, this deadline was extended based on the guidelines set out by the microfinance institution. Participants were not asked to forfeit personal belongings to cover loan payments. Control participants were eligible for the microcredit loan and the *Kickstart* Hip Pump at the end of the 1-year follow-up period.

KickStart water pump and agricultural training: Irrigation technologies have been shown to improve agricultural output. (About KickStart) Recognizing the need for improved agricultural tools for poor farmers in Kenya, Kickstart developed a low-cost irrigation pump. These pumps enable farmers to irrigate their crops year-round avoiding dependence on seasonal rainfall thus capitalizing on higher crop prices in the marketplace. In prior evaluations in Kisumu Kenya, farmers using this hip pump have been able to enjoy up to a ten-fold increase in income (Brandsma 2003; Kihia & Kamau 1999; Stevens 2002; World Bank 2010).

Prior to receiving the microfinance loan, participants in the intervention group received eight training modules. The training modules were delivered to groups of farmers on participant’s farms or at a nearby location by agricultural trainers from Kickstart, the loan officer from *Adok Timo*, and the study coordinator. The agricultural portion of the training included a didactic session and practical demonstrations on sustainable farming techniques, seed selection, soil and water conservation, fertilization and crop rotation, integrated pest and disease management (IPM), pre & post-harvest handling and marketing, the use of the MoneyMaker Hip Pump, and identifying improved market access for selling horticultural products. The field-based practical trainings were based on a training needs assessment and the crops selected by the participants. These trainings focused on plant spacing, seed selection, seed rate, crop combination, and a cost-benefit analysis for each crop selected and IPM. Participants were particularly interested in locally available materials for IPM like wood ash, Mexican marigold and livestock urine in controlling pests on crops to enable them to reduce cost and maximize profits. Participants also conducted a market survey as part of the pre & post-harvest handling and marketing which revealed a large demand in the local markets for green vegetables and watermelon. The intervention participants also had an in-depth training on financial record keeping, the importance on savings and loans, and the basics of group dynamics.

### Intervention model

The primary aim of the pilot study was to test if a multisectoral agricultural intervention improves food security and HIV health outcomes. We hypothesized that the proposed multisectoral agricultural intervention will improve food security, prevent treatment failure, reduce co-morbidities, and decrease secondary HIV transmission risk among PLHIV.

We developed an evidenced-based causal framework (Figure 1) to understand the pathways by which food insecurity negatively impacts health outcomes. Food insecurity negatively impacts health outcomes through nutritional, behavioral, and mental health pathways, which emerge directly from the definition of food insecurity (Weiser et al. 2011). In terms of nutritional pathways, food insecurity has been associated with macronutrient and micronutrient malnutrition (Rose & Oliveira 1997; Lee & Frongillo 2001), and weight loss, low body mass index (BMI), and low albumin have been shown to hasten progression to AIDS and death (Stringer et al. 2006; Zachariah et al. 2006; Johannessen et al. 2008). HIV also increases metabolic requirements (Babameto & Kotler 1997; Macallan et al. 1995) and is associated with diarrhea and malabsorption of fat and carbohydrates (Babameto & Kotler 1997; Kotler et al. 1990; Stack et al. 1996; Fields-Gardner & Fergusson 2004). Lack of food may also impede optimal absorption of certain ARVs (Gustavson et al. 2000; Bardsley-Elliot & Plosker 2000; Food and Agriculture Organization 2010), which may contribute to treatment failure. In terms of behavioral pathways: Food insecurity is an important cause of ART non-adherence and treatment interruptions, (Weiser et al. 2010b; Weiser et al. 2009a; Kalichman et al. 2010a; Weiser et al. 2009d); Tuller et al. 2010) which are both well-known determinants of HIV treatment outcomes (Parienti et al. 2004; Parienti et al. 2008; Oyugi et al. 2007). In addition to ART non-adherence and treatment interruptions, as a result of competing demands between food and other resources, food insecure individuals often miss scheduled clinic visits, and may be less likely to initiate ART (Weiser et al. 2010b; Tuller et al. 2010; Weiser et al. 2012). In terms of mental health pathways, food insecurity has been associated with depression and poor mental health status in sub-Saharan Africa and elsewhere, (Weiser et al. 2009c; Tsai et al. 2011; Anema et al. 2011) which in turn have been shown to independently contribute to lower ART adherence and worse HIV clinical outcomes (Ickovics et al. 2001; Tucker et al. 2003; Evans et al. 2002; Weiser et al. 2004). Food insecurity and poverty also contribute to lower levels of empowerment, including women’s empowerment, which can negatively impact health outcomes for HIV. For example, in Uganda, among HIV-infected women low sexual relationship power is associated with malnutrition (Siedner et al. 2012), depression (Hatcher et al. 2012), and worse virologic outcomes (Weiser et al. 2010a, b).

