	Agricultural measures	Agricultural measures were adapted from outcome evaluations developed by Kickstart in Kenya and supplemented by outcome indicators found in an earlier pilot study and a rural assessment. These measures were designed to evaluate uptake and adoption, and to measure changes in agricultural practices including crop diversity and agricultural practices and production. In addition, we evaluated the effectiveness of the training, and specific topics within, so as to refine the training for the subsequent larger cluster-randomized trial.	Quarterly
	Household economic indicators	A modification of the World Bank Living Standards Measurement Study (LSMS) questionnaire (Grosh & Glewwe 1998) was used to measure: a) expenditures (food, health, education and productive investments); b) consumption (food and non-food); c) income (from agriculture and all sources); and d) inter-household commodity and cash transfers.	Quarterly
**Behavioral Outcome**	Risky sexual behaviors	The primary transmission risk outcome was unprotected sex. Other outcomes included: number of non-spousal/non-cohabiting sexual partners, sex-exchange (exchanging sex for money, food, or other resources) Dupas & Robinson 2010); Robinson & Yeh 2011).	Semi-annually
**Health Outcomes**	HIV-related mortality	Burial permits and information from family members were used to determine cause of death.	As needed
	Viral load suppression	Viral load testing was performed on venous blood on the COBAS TaqMan HIV viral load platform (Roche Molecular Diagnostics, Pleasanton, CA) with a lower limit of detection of <20 copies/mL.	Semi-annually
	CD4 Count	We abstracted data for CD4 counts from participant’s medical records. Absolute CD4 count testing was performed on whole blood using the BD FACSCount (BD Bioscience, San Jose, CA).	Semi-annually
	HIV morbidity	HIV morbidity was measured through key outcomes from the medical record. We abstracted data every 3 months for ART treatment interruptions and episodes of opportunistic infections. We also gathered self-report data on opportunistic infections and symptoms during structured interviews.	Quarterly/Semi-annually
	Physical health	Health status was measured using the MOS-HIV, a tool for assessing health-related quality of life (Wu et al. 1991) that has been validated in resource-limited settings (Chatterton et al. 1999; Mast et al. 2004).	Semi-annually

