#### Analysis of outcome data

This pilot was not powered for formal significance testing of the intervention effect on primary health, behavioral and gender empowerment outcomes. Rather, analyses will focus on assessing the effects of the intervention on proximal mediating factors (Figure 2), and separately on primary outcomes. Analyses for mediating variables will generally treat scores as continuous measures. For example, food security will be measured using the Household Food Insecurity Access Scale (HFAIS) score at the 1-year visit; change in household economic indicators over the 1-year follow-up period will be measured by subtracting baseline from 1-year follow-up data for household expenditures, consumption and income (from agricultural and other sources). Initial comparisons will be based on group-specific descriptive summaries of observed outcomes and rank-based tests comparing outcomes between groups. We will also use regression methods to compare outcomes between groups and control for baseline characteristics. Analyses for primary health outcomes will proceed similarly, with appropriate choices of model for outcome type. For example, we will use pooled logistic regression for between-group comparisons of rates of viral load suppression, and mixed effects regression to compare changes in CD4 counts between groups. We will also make preliminary assessments of degree of mediation in models for primary outcomes via inclusion of mediating factors, with assessment of direct and indirect intervention effects of key mediating variables (Petersen et al. 2006). Finally, we will also perform intent-to-treat and per-protocol analyses of the pilot data, with the per-protocol subset limited to participants that obtained and used the intervention consistently over the 12-months of follow-up. Although these analyses will likely be underpowered for formal testing purposes, the resulting estimates and confidence intervals will be important for planning for the subsequent RCT.

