## Discussion

This pilot study was designed to determine the acceptability and feasibility of the intervention and control conditions, and to determine the preliminary impact of the intervention on mediating outcomes (food security, and household economic indicators). In the baseline evaluation of *Shamba Maisha*, we demonstrated that screening and enrollment into the intervention and control groups was rapid. Enrollment of the 140 participants took only four months, and the screening to enrollment ratio was similar between study arms. Thus, patients at the two study facilities were interested to screen and enroll in the study, i.e. enrollment into the control conditions did not appear to mitigate interest in study participation. This finding has important implications in regards to feasibility for advancing the intervention into a phase 3 cluster randomized controlled trial.

We found that the participants in the intervention and control groups were relatively similar demographically. However, participants at the control site reported a higher household income and dietary intake of vegetables and various protein sources. Importantly, participants in the control group were more likely to have an HIV-1 viral load below the limit of detection than participants enrolled in the intervention group. Self-reported ART non-adherence was uncommon in both groups. The lower proportion of non-detectable plasma viral loads in the intervention group may be related to the fact that the intervention group was economically worse off at baseline, and other studies have shown that markers of lower socioeconomic status are associated with delayed entry into care and worse HIV outcomes. In prior clinical programs in sub-Saharan Africa, viral load suppression ranges from 18% - 41% in observational studies (Hassan et al. 2014; Liegeois et al. 2012; Anude et al. 2013). Thus, our findings are relatively consistent with these results. Of note, this pilot study was not powered or designed to detect differences in viral load suppression by study arm. Rather the future trial will address variability and heterogeneity by randomizing approximately eight matched pair cluster (16 sites). We plan to match sites on a variety of criteria including sociodemographic factors, average rainfall, soil type, access to predominant source of surface water for irrigation (lake, vs. river, vs. shallow wells) and facility type (dispensary, vs. health center, vs. hospital).

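### The stated primary aim is a test of efficacy, which the article's other aim statements contradict and a design with one site per arm cannot deliver

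*Protocol article*

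**What the plan says.** The protocol article describes the purpose of the pilot in four places.

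- **Methods, Intervention model:** "The primary aim of the pilot study was to test if a multisectoral agricultural intervention improves food security and HIV health outcomes". The hypothesis that follows is that the intervention "will improve food security, prevent treatment failure, reduce co-morbidities, and decrease secondary HIV transmission risk among PLHIV".
- **Background, last paragraph:** "we aimed to explore the acceptability and feasibility of the intervention and control conditions", together with a look at preliminary impacts. The same paragraph opens with language about testing the impact on HIV health outcomes and risk behaviours, so it points both ways.
- **Methods, Analysis of outcome data:** "This pilot was not powered for formal significance testing of the intervention effect on primary health, behavioral and gender empowerment outcomes". The section nevertheless plans between-group tests: "Initial comparisons will be based on group-specific descriptive summaries of observed outcomes and rank-based tests comparing outcomes between groups". Regression comparisons follow, and the health outcomes are to be handled in a similar way. It closes by calling the analyses probably underpowered for formal testing and by giving the estimates and confidence intervals a planning role.
- **Discussion, first two paragraphs:** the purpose is given as feasibility and acceptability, and its effect part covers mediators only: "to determine the preliminary impact of the intervention on mediating outcomes (food security, and household economic indicators". HIV health outcomes are absent from that statement. The second paragraph adds that the pilot was neither powered nor designed to find a difference between arms in viral suppression.

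The Randomization section states that one site was allocated to intervention and one to control. Enrolment was 72 and 68 participants.

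**The concern.** A primary aim tells the reader what the trial's result will be judged against. Here it promises an answer on efficacy in two domains, food security and HIV health. Three other sections promise something more modest, and one of them expressly says that viral suppression, a central HIV health outcome, is not something the pilot was designed to detect.

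At stake is what may be concluded at the end. If the Intervention model wording governs, a nominally significant rank test or regression coefficient can be written up as meeting the primary aim. If the other sections govern, the same result is a preliminary estimate for planning. The article should not leave that choice open, least of all when the design cannot support the first reading.

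**Working it through.** The article states no alpha, effect size or sample-size derivation for the outcomes, so there is no design figure to reproduce. The check compares the passages and then asks what two sites can show.

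**Step 1. The statements side by side**

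| Section | Purpose | Food security | HIV health outcomes |
|---|---|---|---|
| Intervention model | Test of efficacy | Yes | Yes |
| Background | Feasibility, acceptability, preliminary impact (after opening with test language) | Within outcomes of interest | Within outcomes of interest |
| Analysis of outcome data | Estimates and intervals for planning | Mediator, analysed | Analysed, power disclaimed |
| Discussion | Feasibility, acceptability, preliminary impact | Yes, as mediator | Not in the purpose; viral suppression expressly excluded |

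The first row cannot be reconciled with the third and fourth.

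**Step 2. Is lack of power the whole answer?** No. The opening power disclaimer covers the health, behavioural and empowerment outcomes. Food security, half of the stated aim, is not in that sentence. If participants were independent, with an assumed two-sided 5% level and 80% power, the detectable standardised difference would be (1.960 + 0.842) × √(1/72 + 1/68) = 2.802 × 0.1691 = 0.47. A moderate effect on food security would then be detectable, so the decisive obstacle for that half of the aim is the number of sites.

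**Step 3. What two sites can show**

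- Degrees of freedom for variation between sites within arms: 2 sites − 2 arms = 0. That variation cannot be estimated, and a site term is indistinguishable from the arm term.
- Only two allocations were possible, each with probability 1/2. Swapping them changes the sign of the arm difference but not its size, so the smallest two-sided randomisation p-value is 2/2 = 1.
- The sites already differed before treatment: mean monthly household income $104 vs $273, and detectable viral load 49% vs 28% (Table 2).

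**Step 4. Size of the problem if site is ignored (illustration)**

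Inputs: m = 140/2 = 70 participants per site; assumed two-sided level 5%; assumed intraclass correlation (ICC) of 0.01 to 0.05. The article gives neither the level nor the ICC.

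Design effect D = 1 + (m − 1) × ICC. True error = 2 × [1 − Φ(1.96/√D)].

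| ICC | D | 1.96/√D | True error |
|---|---|---|---|
| 0.01 | 1 + 69 × 0.01 = 1.69 | 1.51 | 13% |
| 0.02 | 1 + 69 × 0.02 = 2.38 | 1.27 | 20% |
| 0.05 | 1 + 69 × 0.05 = 4.45 | 0.93 | 35% |

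Even one outcome, chosen in advance and tested once, would not hold its nominal level.

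**The case against.** **The article already disclaims confirmatory intent.** Background, analysis section and Discussion are broadly compatible, and the Intervention model sentence is the outlier. The closing sentence of the analysis section can be read as covering the whole plan, and the Discussion lists the two-site design as a limitation that calls for replication. Most of this stands. It reduces the point to a correction of the aim, and it also shows which statement should give way.

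**The plan adjusts for baseline characteristics.** True, but adjustment deals with measured baseline differences. It cannot remove unmeasured site differences or those that arise during follow-up, such as local weather.

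**A lead contrast is largely present.** The analysis section says it focuses on proximal mediators and ties the food insecurity score to the one-year visit. That helps, but the score is offered as an example and is not designated the main estimate.

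**A stronger inference to resist.** A reader might infer that the plan has a multiplicity defect: many outcomes tested with no hierarchy, so that any chance result meets the aim. The documents do not support this.

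- A missing hierarchy or alpha split is no defect in an article about a pilot. It may also stand in the full protocol or analysis plan, which are not shown.
- Expenditure, consumption, income and empowerment lie outside the aim as worded. Of the outcomes named in the analysis section, only the food insecurity score, viral suppression and CD4 count fit it. At an assumed independent 5% each, the chance of at least one false positive is 1 − 0.95³ = 14%, and of a favourable one 1 − 0.975³ = 7%.
- The aim joins its two domains with *and*. If both must be met, the risk falls instead of rising.
- The usual comparator, 2.5% in the favourable direction for a single contrast, does not hold with one site per arm (step 4).

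**Conclusion.** The primary aim in the Intervention model section is wrong as worded. It contradicts the purpose given in the Discussion, the feasibility aim in the Background and the power disclaimer in the analysis section. It also claims a test that one site per arm cannot provide.

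The contradiction and the confounding of site with arm follow from the article alone. The error rates of 13% to 35% are illustrations that rest on an assumed 5% level and assumed ICCs of 0.01 to 0.05. The point does not depend on how many outcomes are tested, and family-wise error figures should not be used to argue it. The planned analyses may stay; what must change is the claim that can be drawn from them. The change should be made, but it corrects wording and does not call for a redesign.

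**What to change.** 1. **Intervention model:** state that the primary aim is feasibility and acceptability, with preliminary estimation of effects on the proximal mediators. Replace *to test if* by *to estimate*, and bring the test language at the start of the last Background paragraph into line.
2. **Analysis of outcome data, main estimate:** name the between-arm difference in the food insecurity score at 12 months, intent-to-treat, as the main effect estimate. Say that it is not a confirmatory test, because site and intervention effects cannot be separated.
3. **Analysis of outcome data, all comparisons:** state that every between-group comparison is exploratory, is reported as an estimate with a confidence interval, and supports no efficacy claim from its p-value.

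**Cost:** wording only, with no new data or participants. A nominally significant result can no longer be presented as meeting the primary aim. Because the Discussion already refers to follow-up at trial close, the choice of main estimate should be dated, with a statement of whether outcome data had been seen, and not described as prespecified unless an earlier document shows it.
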